#### Secondary outcomes

Visual analogue pain score (VAS) pain score at days 1, 5–7, 30 days and 1 year post-operative. A preoperative VAS score will also be recordedSeroma formation (no fixed time point) (a seroma will be defined as any clinically apparent fluid collection at the site of mesh placement and classified as per the European Hernia Society classification system)The length of postoperative hospital stayThe time to return to normal daily activityWound infectionOperating timeMesh fixation time after adhesions have been taken down and fascia closedHernia recurrence at one year and at all time pointsHealth-related quality of life - assessed using the Short Form 36™ (pre-operatively, 30 days and 1 year), and the Carolinas Comfort Score™ (which is specifically designed for hernia repair) (at 30 days and 1 year).Adverse events.

Wound and pain assessments at all time-points will utilise a standardised proforma. These wound assessment tools will be pre-validated on patients undergoing any abdominal surgery in the unit for reproducibility and ease of use prior to full trial launch.

### Statistical analysis

All analyses will be pre specified prior to data collection and conducted according to the intention-to-treat principle and presented in accord with CONSORT guidelines for the reporting of RCTs. All analyses will be conducted using R v3.0.2. All statistical tests will be 2-sided, and deemed to be statistically significant if *p* ≤ 0.05. The analyst will be blind to group allocation.

The primary outcome, VAS pain scores at day 30, will be explored via descriptive statistics and graphics. The scores in each of the groups will then be compared using an ANOVA with study group and defect size as factors. Secondary analyses will report all outcomes at each time-point using appropriate (parametric/non-parametric) descriptive statistics (frequencies [%] or mean/median [standard deviation (SD)/interquartile ranges (IQR)]) and graphics. The pre-operative variables will also be described via these methods.

VAS scores over time will be explored via a generalised linear model, using time, group and an interaction term as covariates. Operation time, mesh time, length of stay and time to return to normal daily activities will be compared between groups using descriptive statistics and independent t-test or Mann-Whitney U test as appropriate. Descriptive comparisons will also be made between the two defect size groups for each outcome. For secondary outcomes consideration for multiple testing will be included in the conclusions. Total numbers with any of seroma formation, wound infections or hernia recurrence at 30 days and 1 year will be reported with odds ratios.

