### Study process

Following potential participant identification and recruitment from incisional hernia referrals in participating surgeons’ out-patient clinics the potential participant will be sent information about the study. A Patient Information Sheet (PIS) will be given to the participant as soon as the decision has been made to list the patient for incisional hernia repair. In all cases, patients will be given sufficient time to consider the implications of their participation (minimum of one week). Written informed consent to participate in the study will be obtained preoperatively, at the same setting where (normal) consent for the intended surgical procedure is obtained > 24 h prior to surgery, by the operating surgeon. Intraoperatively, the size of the hernia defect will be photographed next to a metric ruler as per the Surgeon’s Instructions. Standardised post-operative care will be used in keeping with the Surgeon’s Instructions. Pain assessments will be conducted at pre-operation then post operatively on days 1, 5–7, day 30 (primary end point) and 1 year.

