### Trial randomisation

There will be two arms to the trial (*n* = 136):Mesh placement with absorbable tack fixation.Mesh placement with non-absorbable tack fixation.

Participants will be allocated in sequence to a unique identification number and randomised to one of two groups i.e. receive either absorbable or non-absorbable tack fixation, stratified by defect size (3-6 cm or > 6-10 cm). The participant randomisation procedure is shown below.

Patients who have given consent and are due to be operated on will be randomised by a sealed envelope randomisation.

The operating surgeon will select from the sealed envelopes the tack to be used for the TACKoMESH Trial on the morning of the patient’s planned surgery to obtain the randomisation allocation to treatment. The patient’s initials and date of birth will be entered into the randomisation allocation; a study number and the treatment allocation assigned to each patient. The study number and treatment allocation will automatically appear on the Study Randomisation Form. Following the appropriate procedure the completed online Study Randomisation Form will be printed by the operating surgeon, placed in a provided sealed envelope, and labelled as ‘TACKoMESH - Study Randomisation Form and Incisional Hernia Repair Operation Note’.

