### Sample size

Primary outcome: Pain score at rest and activity at day 30 recorded using visual analogue pain score (VAS) (0–10).

Previous studies indicate that a good approximation for the standard deviation (SD) in VAS is 2. With an alpha of 0.05, 80% power and 20% dropout, a sample size of 74 (37 per group) is sufficient to detect a difference of 1.5 between the groups.

There has been a suggestion that a rate of attrition of 20% is un-necessarily high for this group of patients, and we also consider whether the difference is achievable, therefore we recalculate the sample size considering these changes:

With a power of 80%, an alpha of 0.05, SD 2 and dropout of 5%, a sample size of 136 (68 per group) is sufficient to detect a difference of 1 between the groups.

No interim analysis will be undertaken therefore no adjustment is required in the sample size. This is a fixed design and no sample size re-estimation will be performed during the course of the study.

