### Outcomes

#### Primary outcome

Pain score at rest and activity at day 30 recorded using visual analogue pain score (VAS) (0-10 cm).

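### The primary day-30 comparison leaves out the pre-operative VAS that the trial records, and so gives up precision that is available at almost no cost

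*Protocol article*

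**What the plan says.** All references are to the protocol article.

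- **Primary outcome:** "Pain score at rest and activity at day 30 recorded using visual analogue pain score (VAS", on a 0 to 10 scale.
- **Statistical analysis, primary model:** the groups are to be "compared using an ANOVA with study group and defect size as factors". No other term is named.
- **Study process:** "Pain assessments will be conducted at pre-operation then post operatively on days 1", followed by the later visits. The list of secondary outcomes also mentions a pre-operative VAS, in the singular.
- **Statistical analysis, baseline data:** "The pre-operative variables will also be described via these methods", that is, by descriptive statistics and graphics.
- **Statistical analysis, repeated measures:** "VAS scores over time will be explored via a generalised linear model, using time, group and an interaction term as covariates". This model is secondary to the day-30 comparison.
- **Trial randomisation:** allocation is "stratified by defect size (3-6 cm or > 6-10 cm"). Baseline pain is not a stratification factor.
- **Sample size:** "With a power of 80%, an alpha of 0.05, SD 2 and dropout of 5" per cent, the plan takes 136 patients (68 per group) to detect a difference of 1.

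**The concern.** The outcome variable is measured before treatment, on the same scale, and is then left out of the primary comparison. The article names the terms of the primary model, so this is a stated choice and not a detail left to a statistical analysis plan that we have not seen.

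If pre-operative pain predicts day-30 pain at all, part of the SD of 2 is explainable variation that the ANOVA leaves in the error term. Removing it narrows the confidence interval without recruiting anyone. What is at stake is the precision of the main result in a trial sized to meet 80% power and no more.

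**Working it through.** **Inputs from the protocol article.** Difference 1, SD 2, power 80%, alpha 0.05 and dropout 5% (Sample size); two-sided tests, "All statistical tests will be 2-sided" (Statistical analysis).

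**Assumed input.** r, the correlation between pre-operative and day-30 VAS. The documents do not give it, so it is shown from 0 to 0.5.

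**Step 1: reproduce the plan's figure.** By normal approximation, n per arm = 2 × (1.960 + 0.842)² × 2² / 1² = 62.8, so 63. The exact two-sample t-test needs 64. Allowing for dropout, 64 / 0.95 = 67.4, rounded up to 68 per arm, or 136 in total. The plan's figure is reproduced exactly. (The normal approximation gives 63 / 0.95 = 66.3, so 67 per arm and 134 in total.)

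**Step 2: effect of adjusting.** Residual SD = 2 × √(1 − r²), and the variance falls by r². Power is for a two-sided t-test with 64 per arm and a true difference of 1. The detectable difference at 80% power is residual SD × √(2/64) × (1.960 + 0.842).

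| r (assumed) | Variance cut | Residual SD | Power | Detectable difference |
|---|---|---|---|---|
| 0 | 0% | 2.00 | 80.1% | 0.99 |
| 0.1 | 1% | 1.99 | 80.5% | 0.99 |
| 0.2 | 4% | 1.96 | 81.7% | 0.97 |
| 0.3 | 9% | 1.91 | 83.7% | 0.95 |
| 0.4 | 16% | 1.83 | 86.5% | 0.91 |
| 0.5 | 25% | 1.73 | 90.0% | 0.86 |

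**Step 3: price of the covariate.** The adjustment uses one degree of freedom, which lowers power by less than 0.01 percentage points at r = 0. Estimating the slope also inflates the expected variance by a factor of about 1 + 1/(128 − 4) = 1.008. That takes a further 0.2 to 0.3 percentage points off each adjusted figure: 79.8% at r = 0, 80.2% at r = 0.1 and 89.8% at r = 0.5. Adjustment therefore roughly breaks even at r = 0.1 and gains above it. The most it can lose is about 0.3 points.

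**Step 4: is chance imbalance a second problem?** Assume that the pre-operative SD is also 2, which the documents do not state. The standard error of the baseline mean difference is then 2 × √(2/64) = 0.354. With equal SDs the slope equals r, so at r = 0.5 an imbalance of one standard error moves the day-30 difference by 0.5 × 0.354 = 0.177. As a share of the unadjusted variance this is 0.177² / 0.354² = 0.25, which is the 25% already in the table. It is the same gain and should not be counted twice.

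**The case against.** The strongest reply is that nothing here is broken. The ANOVA includes the only stratification factor. Under randomisation it is unbiased, with a 5% type I error overall, and the sample size was built for an unadjusted SD of 2. All of that stands.

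The second reply is that the size of the gain rests on an unknown. Pre-operative VAS reflects the hernia, whereas the protocol links post-operative pain to the tacks, so the carry-over may be modest. This also stands, and it is why the table starts at r = 0. It argues for modesty about the benefit. It does not argue for leaving the covariate out, because the possible loss is a fraction of a percentage point.

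Three stronger readings are tempting, and the documents do not support them.

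- *A reader might infer that the trial is underpowered.* It is not: 136 reproduces exactly for the planned test.
- *A reader might infer that chance imbalance biases the result or inflates the type I error.* If the observed imbalance lay at its 95% limit (1.96 × 0.354 = 0.69 points, baseline SD 2), the unadjusted test's conditional error rate would be about 8% at r = 0.3 or 13% at r = 0.5. Averaged over all possible imbalances it is 5%, and the unadjusted confidence interval already allows for this.
- *A reader might infer that the pre-operative VAS is never analysed.* The secondary model of VAS over time may include that visit. It would not alter the primary comparison.

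**Conclusion.** The point holds as a missed gain in efficiency. The primary comparison is valid and meets its stated power, but it does not use a baseline measurement that the trial takes. With 64 evaluable per arm, a difference of 1 and SD 2, power would move from 80% to between about 81% (r = 0.1) and 90% (r = 0.5), less 0.2 to 0.3 points for estimating the slope.

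That the covariate is omitted is certain from the text. How much it would help is not, because it depends on a correlation that the documents do not give: little at 0.2 or below, and material from about 0.4. The calculation also assumes a linear relation with the same slope in both arms, and attrition at the planned 5%.

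**What to change.** Amend the primary analysis, by a dated and documented change made before unblinding, to an ANCOVA of day-30 VAS on study group, defect-size stratum and pre-operative VAS. Use the matching rest or activity score if both are recorded before surgery. The article mentions only one pre-operative score, so if there is just one, use it for both. Report the adjusted mean difference with its 95% CI, keep the planned ANOVA as a sensitivity analysis, and leave the sample size at 136.

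The cost is a change of wording and one degree of freedom. No further patients or measurements are needed. The amendment does have to be formal: the article says that analyses are specified before data collection, and the trial was registered retrospectively, so enrolment may already have begun. No interim analysis is planned and the analyst is blind to allocation, so the change can be made without knowledge of the results by group. The same change after unblinding would look data-driven.

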#### Secondary objectives

To examine changes in pain using VAS at days 1 and 6, 30 days and one year post-operation at rest and activity.To detect the presence of intermittent hyperaesthesia, burning sensation and or jabbing pain in the abdominal wall.To compare whether the method of fixation for an IPOM repair has an effect on the following outcomes (complications will be classified according to the Clavien Dindo):
Seroma formation at 30 days post operationLength of postoperative hospital stayOperating timeMesh fixation timeWound infection (SSI)Hernia recurrence at 1 yearTime to return to normal daily activity and workHealth related quality of life (QoL)Other adverse events

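### The model named for VAS over time makes no allowance for repeated scores on the same patient; as written, its group-by-time test is too conservative (secondary analysis, should fix)

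*Protocol article*

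**What the plan says.** The Statistical analysis section of the protocol article states: "VAS scores over time will be explored via a generalised linear model, using time, group and an interaction term as covariates". Nowhere does the article mention a patient-level term, a random effect, GEE, a repeated-measures covariance or a robust variance.

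The data for this model are repeated measurements. The Study process section says: "Pain assessments will be conducted at pre-operation then post operatively on days 1, 5–7, day 30 (primary end point) and 1 year". That is four postoperative scores per patient, or five with the preoperative score. The first secondary objective is "To examine changes in pain using VAS at days 1 and 6, 30 days and one year post-operation at rest and activity".

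The significance rule is general: "All statistical tests will be 2-sided, and deemed to be statistically significant if" p ≤ 0.05. On multiplicity the section says: "For secondary outcomes consideration for multiple testing will be included in the conclusions". The primary analysis is separate and uses day 30 only: "The scores in each of the groups will then be compared using an ANOVA with study group and defect size as factors".

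**The concern.** In its ordinary meaning, a generalised linear model assumes independent observations. Scores from one patient at several visits are not independent, so the standard errors from the stated model are wrong. The direction depends on the term. Contrasts within patients (change over time, and group differences in change) get standard errors that are too large. Averages over a patient's visits get standard errors that are too small.

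The Abstract says the trial will establish whether absorbable tacks give less pain both immediately and in the long term. Outside day 30, this model is the only formal between-group comparison of VAS that the Statistical analysis section names. The other VAS reporting at those times is descriptive, and the t-test or Mann-Whitney sentence covers operation time, mesh time, length of stay and return to activity. A real difference in pain trajectory between the arms could therefore be missed because of the model, not because of the data.

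**Working it through.** **Inputs from the protocol article.** SD 2, two-sided alpha 0.05, 80% power, 5% dropout, difference of 1 on the VAS (Sample size); T = 4 postoperative scores, or 5 with the preoperative one (Study process).

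**Assumptions.** The article gives no within-patient correlation, so a common correlation rho of 0.3, 0.5 and 0.7 is used. SD 2, given for the sample size at day 30, is applied at every visit. One VAS score per visit is modelled, with complete data on 64 per arm.

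**Step 1: the plan's own figure.** The article says "a sample size of 136 (68 per group) is sufficient to detect a difference of 1 between the groups". A two-sample t-test with difference 1 and SD 2 needs 63.8, so 64 per arm. 64 / 0.95 = 67.4, so 68 per arm and 136 in total. The figure reproduces, and it gives the 64 per arm used below.

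**Step 2: ratio of true to model standard error when scores are treated as independent.**
- Group effect averaged over T times: sqrt(1 + (T − 1)·rho)
- Group-by-time contrast: sqrt(1 − rho)

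The true size of a nominal 5% one-degree-of-freedom test is 2·(1 − Phi(1.96 / ratio)).

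**Step 3: group-by-time interaction.** For the joint 3-df test with T = 4, the large-sample size is P(chi-square on 3 df > 7.815 / (1 − rho)).

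| rho | single contrast: ratio | size | joint test: formula | joint test: simulated |
|---|---|---|---|---|
| 0.3 | sqrt(0.7) = 0.84 | 1.9% | 1.1% | 1.0 to 1.5% |
| 0.5 | sqrt(0.5) = 0.71 | 0.6% | 0.14% | 0.2 to 0.25% |
| 0.7 | sqrt(0.3) = 0.55 | 0.03% | under 0.01% | 0 rejections |

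The simulations fitted an ordinary Gaussian model to 4,000 trials per setting. The ranges are from two codings of categorical time, which give the same joint test, so the spread is simulation error. With time entered linearly in days, the interaction test was also conservative: 2.2%, 0.6% and 0.05%.

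**Step 4: power cost.** Take a difference of 1 between the arms in the change between two visits.
- Model SE = 2·sqrt(2)·sqrt(2/64) = 0.50.
- True SE at rho 0.5 = 2·sqrt(2 × 0.5)·sqrt(2/64) = 0.354.
- Power with the correct SE: Phi(1/0.354 − 1.96) = 81%.
- Power under the stated model: 1 − Phi((1.96 × 0.50 − 1)/0.354) = 52%.

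At rho 0.3 the pair is 67% and 52%; at rho 0.7 it is 95% and 53%.

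**Step 5: group term.** This depends on which test is read from the output.

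| rho | time-averaged effect, T = 4: ratio | type I error | simulated | T = 5, formula |
|---|---|---|---|---|
| 0.3 | sqrt(1.9) = 1.38 | 15.5% | 15.5% | 18.6% |
| 0.5 | sqrt(2.5) = 1.58 | 21.5% | 21.6% | 25.8% |
| 0.7 | sqrt(3.1) = 1.76 | 26.6% | 25.3% | 31.5% |

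With reference-coded categorical time, the group coefficient is the group difference at the reference visit only. Its simulated type I error at these correlations was 4.4% to 5.6%. At rho = 0 all tests were near 5%, as they should be.

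**The case against.** The strongest reply is that the sentence lists fixed effects and does not say that scores are treated as independent. Covariance structure is a detail that a condensed article may leave to the full protocol or SAP, and the authors may have meant a mixed or repeated-measures model. This stands in part: the intention cannot be known from the article. But the article does not simply stay silent. It names a model class and lists its terms, and that model does not suit repeated scores. If a mixed model was meant, the sentence needs the same correction.

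A second reply is that the analysis is secondary, described as exploratory, and that its sure consequence is lost power and not a false claim. This stands, and it limits the severity.

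A reader might also infer more than the article supports:
- *That the model will declare group differences far too often.* The article names no time-averaged test. The inflation arises only if one is made, or if the group coefficient is read with time entered linearly. Reference coding is R's default for factors, R is the named software, and under that coding the coefficient stays near 5%.
- *That time enters as a straight line, so the 1-year score dominates.* The article does not say so. The same sentence calls group a covariate, and group is categorical, so the word does not imply continuous time.
- *That leaving out the defect-size stratum or the preoperative score is an error.* Including them is sensible and matches the primary analysis for the stratum, but it is an improvement and not a correction.

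**Conclusion.** The point holds as a should-fix on a secondary analysis. As written, the model ignores within-patient correlation, and for any positive equal correlation the group-by-time test is too conservative under every time coding tried. At the assumed correlations of 0.3 and 0.5, its joint size is about 1 to 1.5% and 0.1 to 0.25% instead of 5%. Power for a difference of 1 in change falls from 67% and 81% to about 52%. Inflation of the group test to roughly 16 to 27% is conditional on a time-averaged effect being tested.

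All sizes rest on assumed correlation, equal variance across visits and complete data. The direction of the interaction error does not depend on the particular positive correlation chosen. The day-30 ANOVA uses one score per patient for each comparison, so neither it nor the sample size of 136 is affected.

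**What to change.** Replace the sentence on VAS over time with wording such as: *Postoperative VAS scores (days 1, 5–7 and 30, and 1 year) will be analysed with a linear mixed model for repeated measures with an unstructured within-patient covariance, or by GEE with robust variance. Terms will be group, time as a category, group by time, preoperative VAS and defect-size stratum. Group differences with 95% confidence intervals will be reported at each time.*

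If a model of this kind was already intended, stating the patient-level term or covariance structure is enough to remove the error. The change costs one sentence and standard R code. The preoperative VAS and the defect-size stratum are already collected, and no extra patients or visits are needed. It should be made before the data are analysed.

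### Four secondary time outcomes are tested without the defect-size stratum used in randomisation and in the primary ANOVA, so precision and power are lost if defect size predicts them.

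*Protocol article*

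**What the plan says.** Under Trial randomisation, the article says patients "receive either absorbable or non-absorbable tack fixation, stratified by defect size", with two levels: "stratified by defect size (3-6 cm or > 6-10 cm"). The mechanism is sealed envelopes; neither blocks nor any other restriction within strata is described.

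Under Statistical analysis, day-30 VAS is compared by an ANOVA with study group and defect size as factors. The same section then says that operation time, mesh time, length of stay and return to normal activity "will be compared between groups using descriptive statistics and independent t-test or Mann-Whitney U test as appropriate". For these outcomes defect size appears only in descriptive comparisons between the two size groups. The VAS-over-time model has time, group and their interaction, and no defect-size term. Seroma, infection and recurrence "hernia recurrence at 30 days and 1 year will be reported with odds ratios" (the quoted words name recurrence, the last of the three); no model or test is named for them.

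**The concern.** When randomisation is stratified on a factor that predicts the outcome, the analysis should carry that factor. Otherwise the difference between strata stays in the error term. The treatment estimate remains unbiased, but its interval is wider than it need be. If the allocation also forces balance within strata, the reported standard error exceeds the true sampling error and the test rejects less often than its nominal level.

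It is plausible that defect size predicts some of these outcomes. Under Surgical technique, the fascia is sutured, the mesh must extend a fixed margin past the defect, and tacks follow the outer rim and the closure line. Operation time could therefore rise with defect size through both closure and tacking. For mesh fixation time only mesh size and tack number can act, because Secondary outcomes starts that clock after the fascia is closed.

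At stake is the sensitivity of comparisons that the Discussion presents as informative about the articulating device, fixation time among them.

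**Working it through.** **1. The plan's own figure.** Inputs from Sample size: SD 2, difference 1, alpha 0.05, power 80%, dropout 5%. From Statistical analysis: "All statistical tests will be 2-sided". The two-sample t-test needs 63.77, so 64 per arm; 64/0.95 = 67.4, so 68 per arm and 136 in total. This matches "a sample size of 136 (68 per group) is sufficient to detect a difference of 1 between the groups". The preceding calculation (difference 1.5, dropout 20%) gives 29 per arm; 29/0.80 = 36.25, so 37 per arm and 74 in total, again as stated. The sample size is not in dispute. It supplies the scale: about 130 completers (136 × 0.95 = 129.2) and a standardised difference of 1/2 = 0.5 SD.

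**2. Assumptions not in the documents.** The share of large defects, p, is taken as 0.30. The gap between strata, c, is 0, 0.5, 1.0 or 1.5 within-stratum SD. Outcomes are normal. Allocation is in permuted blocks of 4 within strata.

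**3. Formulas.** With within-stratum variance 1, the total variance is 1 + p(1−p)c².
- Variance explained = p(1−p)c² / [1 + p(1−p)c²]
- Standard error ratio, unadjusted to adjusted = √[1 + p(1−p)c²]
- Under balance, type I error ≈ 2[1 − Φ(1.96 × ratio)]

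With p(1−p) = 0.21:
- c = 0.5: 0.0525/1.0525 = 5%; ratio √1.0525 = 1.03; type I error 4.4%
- c = 1.0: 0.21/1.21 = 17%; ratio √1.21 = 1.10; type I error 3.1%
- c = 1.5: 0.4725/1.4725 = 32%; ratio √1.4725 = 1.21; type I error 1.7%

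**4. Simulation with blocks** (130 completers, 3,000 runs per setting; power is for a difference of 0.5 within-stratum SD):

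| Variance explained | SE ratio | Type I: t | Type I: Mann-Whitney | Type I: adjusted | t-test CI coverage | Power: t | Power: adjusted |
|---|---|---|---|---|---|---|---|
| 0% | 1.00 | 5.0% | 5.3% | 5.0% | 95.0% | 80.4% | 80.3% |
| 5% | 1.03 | 4.4% | 4.0% | 5.0% | 95.6% | 78.1% | 79.5% |
| 17% | 1.10 | 2.8% | 3.2% | 4.6% | 97.2% | 74.5% | 79.7% |
| 32% | 1.21 | 1.6% | 1.6% | 4.6% | 98.4% | 66.8% | 81.0% |

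The Monte Carlo error is about √(0.05 × 0.95/3000) = 0.4 points on a 5% rejection rate, so formula and simulation agree.

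**5. Simulation without blocks.** Over the same four gaps the t-test's type I error is 5.2%, 5.1%, 4.4% and 4.9%, that is, near nominal. Power is still lost: 77.9% against 79.1% adjusted at c = 0.5, and 71.6% against 78.9% at c = 1.0. Power at c = 1.5 was not obtained.

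**6. Sensitivity to the split.** p(1−p) peaks at equal strata. At c = 1.0 the ratio is √1.25 = 1.12 for p = 0.5, 1.10 for p = 0.3 and √1.16 = 1.08 for p = 0.2.

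**The case against.** The strongest reply is that the loss is conditional throughout. The article gives no association between defect size and any of the four outcomes, and with none the ratio is 1.00. It describes no blocks, so conservatism cannot be asserted. Only secondary outcomes are affected, mean differences are unbiased, the primary analysis is already adjusted, and false positives are not inflated. All of this stands and sets the severity.

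A second reply is that a condensed article leaves covariates to the analysis plan. That does not hold for these four outcomes, because the article names the tests and neither has a place for a stratum.

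Two stronger readings are tempting, and the document supports neither.

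- **Odds ratios.** A reader might infer that their intervals are also too wide. The article names no test or model for them. With assumed inputs (130 patients, 40% large defects, baseline risk 20%, stratum odds ratio 3, no treatment effect), the crude log-odds-ratio standard error is 0.386 and that from a logistic model with the stratum is 0.398. Adjustment does not narrow the interval, and it targets a conditional odds ratio, a different quantity. Under exact balance the crude standard error does slightly exceed the true sampling SD (0.386 against 0.374), but that needs the same unstated balance.
- **VAS over time.** A reader might apply the same percentages to this model. They come from a two-sample comparison. A constant stratum effect largely cancels from a group-by-time interaction, and no loss has been shown there.

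**Conclusion.** The point holds as an efficiency point about four secondary outcomes. The stratum that governs allocation and enters the primary ANOVA is left out of the named tests for operation time, mesh fixation time, length of stay and return to normal activity.

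If the stratum explains 5% to 32% of variance, with 30% large defects, the unadjusted standard error is about 3% to 21% larger than the adjusted one. With blocks, t-test power for a 0.5 SD difference is about 78% to 67% where adjustment keeps about 80%. The accompanying fall in type I error, to between 4.4% and 1.6%, rests on balance within strata; without it the error rate stays near 5% and only precision and power suffer. It would go too far to say outright that these tests are conservative, since the article does not establish balance.

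The simulations used normal data, so the figures are indicative for skewed durations. Severity is low.

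**What to change.** Replace the t-test or Mann-Whitney sentence for these four outcomes with a linear model on study group and defect-size stratum, on the log scale where the outcome is skewed. Where a rank test is preferred, use a van Elteren test stratified by defect size. For consistency with the primary ANOVA, defect size may also be added to the VAS-over-time model; this is optional. The odds ratios need no change on this ground.

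The cost is analysis wording and, in the linear model, one degree of freedom. No data, patients or procedures change.
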